#### Control arm

The control group consists of patients randomised to use the regular patient pathway prior to day case outpatient surgery. All these patients are referred to the surgical outpatient clinic. At the outpatient clinic patients are examined by a surgeon, who determines whether surgery is indicated. If so, patients are referred to outpatient surgery and the surgical procedure is performed several weeks after the examination.

#### Objectives

We wish to test the efficacy of the one-stop strategy in decreasing waiting time and increasing the cost-effectiveness of selected day case surgical outpatient procedures. We hypothesise that patients exposed to the one-stop strategy (intervention) will have decreased waiting time and increase the cost-effectiveness for the hospital, compared to patients who use the regular patient pathway, i.e. examination at the surgical outpatient clinic prior to outpatient surgery.

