**Materials and Methods:**

In a randomised controlled trial, selected patients (inguinal hernia, gallstone disease and pilonidal sinus) referred to the university hospital are either randomised to direct electronic referral and booking for outpatient surgery (one stop), or to the traditional patient pathway where all patients are seen at the outpatient clinic several weeks ahead of surgery.

Consultants in gastrointestinal surgery designed standardised referral forms and guidelines. New software has been designed making it possible to implement referral forms, guidelines and patient information in the GP's electronic health record. For "one-stop" referral, GPs must provide mandatory information about the specific condition. Referrals were linked to a booking system, enabling the GPs to book the hospital, day and time for outpatient surgery. The primary endpoints are waiting time and costs. The sample size calculation was based on waiting time. A reduction in waiting time of 60 days (effect size), 25%, is significant, resulting in a sample size of 120 patients in total.

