The newly established Norwegian National Health Network [4] has given us the potential to improve the communication between levels of the health care providers. The National Health Network is intended to support exchange of information and enable affiliated organisations to offer professional support, medical services and administrative services in the network. From a single connection point, users should be able to communicate with all the other participants connected to the network.

The main objectives of the present study were to assess whether standardised electronic referrals based on guidelines and booking of outpatient surgery by the GPs would decrease waiting time and increase the cost-effectiveness of day case outpatient surgery for patients with inguinal hernia, pilonidal sinus and gallstone disease.

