##### Cost-minimisation analysis

We will use a cost-minimisation analysis in this study, since this health care intervention has a similar medical outcome for both groups, i.e. surgical outpatient treatment [5]. The analysis will have a public health provider perspective. This includes travel costs, since the public health service pays for these costs in Norway. Direct health care costs that are the same in both alternatives will be excluded. The costs for the GPs providing this service will include investment, support, and time costs. Costs of traditional referral will include hospital administration, examination at the Surgical Outpatient Department (surgeon time, nurse time), surgical treatment at the Department of Day Case Surgery (surgeon time, anaesthetist time, and nurse time) unused surgical capacity due to incorrect referral, and patient travel costs. All costs will be estimated separately and compared between the two groups.

We will then conduct a threshold analysis. This analysis calculates the number of patients needed to break even, i.e. where the cost of providing a one-stop service equals the cost of traditional referrals.

This value is given by:

Total cost of one-stop service = Total cost of traditional referral

F_OS _+ xV_OS _= F_TR _+ xV_TR_

X = (F_OS _+ F_TR_)/(V_OS _- V_TR_)

X = number of consultations; F = fixed costs; V = variable costs; OS = one-stop; TR = traditional referral;

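### The objectives claim cost-effectiveness, but the economic primary outcome compares costs only and leaves out the waiting-time difference the trial is sized to detect

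*Protocol article*

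**What the plan says.** **Aim and hypothesis.** The Background gives the main objective as whether the intervention "would decrease waiting time and increase the cost-effectiveness of day case outpatient surgery". The Objectives section repeats this ("We wish to test the efficacy of the one-stop strategy in decreasing waiting time and increasing the cost-effectiveness of selected day case surgical outpatient procedures") and hypothesises that one-stop patients "will have decreased waiting time and increase the cost-effectiveness for the hospital". The abstract's Discussion and the opening of the main Discussion also speak of cost-effectiveness. Later the Discussion uses a third term, cost benefit.

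**Endpoint and analysis.** The abstract says: "The primary endpoints are waiting time and costs". Under the primary outcome heading, the Cost-minimisation analysis section says: "We will use a cost-minimisation analysis in this study, since this health care intervention has a similar medical outcome for both groups". It then says: "All costs will be estimated separately and compared between the two groups". A threshold analysis follows, to find the number of patients "where the cost of providing a one-stop service equals the cost of traditional referrals".

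**Waiting time** is a primary outcome of its own. The Sample size section plans for a 60-day difference with a standard deviation (SD) of 120 days.

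**Perspective.** The hypothesis refers to the hospital. The Cost-minimisation analysis section takes the view of the public health provider and includes GP costs and patient travel.

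**The concern.** Cost-effectiveness sets cost against effect, and cost-minimisation is the special case in which the effects do not differ. The protocol supports that case by pointing to a similar medical outcome. Yet the effect the trial is built to change is waiting time, and it is sized on the assumption that this will differ. In discussing an earlier study of direct referral, the protocol itself treats a shorter delay as better quality of care. So the equal-effects premise covers the surgical result but not the effect of main interest.

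The conclusion is at stake in two ways. A faster but dearer one-stop service would look unfavourable in the economic analysis with no measure of what the extra money bought. Conversely, a bare cost saving could be reported as improved cost-effectiveness although no effect entered the analysis.

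**Working it through.** No stated figure in the protocol bears on this point, so the check is one of logic, followed by an illustration.

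**1. Objective against analysis**

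| Place | Economic target |
|---|---|
| Abstract (Discussion), Background, Objectives, Discussion | Cost-effectiveness |
| Abstract (Materials and Methods) | Costs |
| Cost-minimisation analysis | Cost difference, then break-even volume |
| Discussion, on health outcomes | Cost benefit |

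No section describes a quantity that relates cost to waiting time.

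**2. When the two targets agree**

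Let ΔC be the mean cost per patient, one-stop minus traditional. Let ΔW be the mean waiting days saved and λ the value placed on a day saved. Net benefit is NB = λ·ΔW − ΔC. Cost-minimisation looks only at −ΔC, which equals NB when ΔW = 0 or λ = 0.

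- ΔW = 0: NB = −ΔC. Cost-minimisation is a valid test of cost-effectiveness.
- ΔW = 60 and ΔC ≤ 0: one-stop is better on waiting time and no worse on cost. Both approaches favour it.
- ΔW = 60 and ΔC > 0: the sign of NB depends on whether λ exceeds ΔC/60. The cost-only comparison is against one-stop for every ΔC > 0.

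Only the third case is a problem.

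**3. Can the third case arise?**

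From the protocol's equation of total costs, F_OS + xV_OS = F_TR + xV_TR, the cost difference per patient at volume x is

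ΔC(x) = (F_OS − F_TR)/x + (V_OS − V_TR).

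If one-stop has higher fixed costs (GP investment and support) and lower variable costs (no outpatient visit, less travel), then ΔC(x) > 0 for every x below x* = (F_OS − F_TR)/(V_TR − V_OS). Planning a break-even analysis accepts that this region may exist. (The solution printed in the protocol has different signs from this x*. That is a separate point.)

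**4. Illustration with assumed costs**

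From the protocol: 60 per arm, 20% excluded, so 60 × 0.8 = 48 evaluable; gain 60 days; SD 120.

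- Standard error (SE) of ΔW = 120 × √(2/48) = 24.5 days; 95% interval 60 ± 1.96 × 24.5 = 12 to 108.
- With the SD of 154 in Table 2: SE = 154 × √(2/48) = 31.4; interval −2 to 122.

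Assumed, because the documents give no costs: SE of ΔC is 500 units, and cost and waiting time are independent.

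- P(cost comparison favours one-stop) = Φ(−ΔC/500).
- P(NB > 0) = Φ[(60λ − ΔC)/√((24.5λ)² + 500²)].

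For example, with ΔC = 600 and λ = 25: Φ(−1.2) = 12%, against Φ(900/791) = Φ(1.14) = 87%.

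| True ΔC | ΔC/60 | Cost only | NB, λ = 10 | λ = 25 | λ = 50 | λ = 100 |
|---|---|---|---|---|---|---|
| −600 | saving | 88% | 98% | >99% | >99% | >99% |
| 600 | 10 | 12% | 50% | 87% | 97% | 98% |
| 1500 | 25 | 0.1% | 5% | 50% | 87% | 96% |
| 3000 | 50 | 0% | 0% | 3% | 50% | 88% |

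With SD 154 the pattern is the same. For ΔC = 600, NB favours one-stop in 83% of trials at λ = 25 and 93% at λ = 50.

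The two approaches part when one-stop is dearer and λ exceeds ΔC/60. They agree when one-stop saves money, and both disfavour it when λ is well below ΔC/60. The table shows the mechanism; it does not forecast this trial's result.

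**The case against.** The strongest reply is that cost-minimisation was chosen for a stated reason. Both arms receive the same surgery, so lower cost at equal medical outcome is greater cost-effectiveness. The aims are written in general language, while the two places that specify the endpoint (abstract and outcome section) both say costs. Waiting time is tested in its own right, so a reader will see both differences. The threshold analysis already addresses fixed costs at low volume. Removing an outpatient visit and its travel may well make one-stop cheaper.

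Much of this stands, and it rules out two stronger readings. A reader might infer that the plan cannot test its economic hypothesis at all. It can, if effects are equal, and a result that is both cheaper and faster would also support the hypothesis. A reader might also infer that the waiting-time gain is ignored. It is not: it is a primary outcome and drives the sample size. It is absent only from the economic comparison. Nor does the protocol write a rule that any extra cost rejects one-stop.

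What the reply does not answer is the dearer-but-faster case. The break-even volume says when the extra cost disappears, not what a saved day costs before then. Two separate differences also do not give the joint uncertainty that a cost-effectiveness statement needs.

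**Conclusion.** The point holds in a limited form. The objective and hypothesis are about cost-effectiveness, and the planned economic analysis is about cost. The two coincide if waiting time is equal or given no value, and they lead to the same conclusion if one-stop is faster and no dearer. They can diverge only if one-stop is faster and dearer. That case is possible below break-even, given higher fixed and lower variable costs for one-stop, but the documents do not show that it is likely. At the planned effect the missing quantity is ΔC/60 per waiting day avoided.

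No numerical size can be attached to this trial, because costs, their variability and a value per day are all absent from the documents. The percentages above rest on assumed values.

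The perspective also differs between the hypothesis (hospital) and the analysis (public health provider), which affects which costs count. This is a modest defect and is cheap to repair.

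**What to change.** Choose one of two routes.

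1. **Keep the cost-effectiveness objective.** Leave the cost difference and break-even volume as the economic primary analysis. Add to the Cost-minimisation analysis section a supporting analysis that presents the cost and waiting-time differences jointly, either as cost per waiting day avoided or as net benefit over a range of values per day. Net benefit behaves better if the waiting-time interval comes near or crosses zero, as it would with SD 154. Resample each patient's cost and wait together for the interval. Investment and support costs are not patient-level, so vary them in a sensitivity analysis.
2. **Keep costs only.** Restate the objective and hypothesis as waiting time and costs in the abstract, Background, Objectives and Discussion, and draw no cost-effectiveness conclusion.

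In either case, state one economic perspective throughout.

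The second route costs only wording. The first needs a little more analysis and no extra patients or visits, since waiting time is already calculated for each individual and costs are already to be estimated in both groups. Its small drawback is that results must be shown over a range of values per day, because the protocol gives no agreed value. For that reason the joint analysis should be supporting and not primary.

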#### Outcome measures

##### Primary outcome

##### Waiting time for outpatient surgery

This time interval will be calculated retrospectively and compared between the two groups. The waiting time specified by health authorities is unreliable (Table 1); waiting time must therefore be calculated separately for each individual using dates from the electronic health record. This will consist of the following dates: the date the referral is noted in the hospital electronic health record, the date of outpatient examination (for the control group) and the date of outpatient surgery.

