##### Intervention

The one-stop strategy is a set of interventions directed at GPs referring patients to the University Hospital. The interventions include: Guidelines for referral, standardised electronic referrals, booking for outpatient surgery and a patient information form.

Guidelines for referral: Guidelines for inguinal hernia, sinus pilonoidalis and gallstone disease were developed (Figure 3). All surgeons performing the surgical procedures reviewed the giudelines, and after a three-month period consensus was reached. The guidelines consisted of signs and symptoms for the condition, indications and contraindications for surgery, necessary blood samples and radiological examinations prior to surgery (for gallstone disease). Photographs of the condition were included in the guidelines for sinus pilonoidalis and inguinal hernia. These guidelines were implemented in the GPs electronic health record.

Standardised referral forms: Standardised referral forms were developed by specialists in gastrointestinal surgery in cooperation with GPs (Figure 2). These referral forms consisted of three parts: information needed for anaesthesia (mandatory), information needed for surgeons (mandatory) and additional information provided by the GPs. These referral forms were implemented in the GPs' electronic health records (Profdoc Winmed).

Booking of time, date and hospital for surgery: The booking system is integrated in the electronic health record (Profdoc Winmed); booking is done at the same time as referral. Patients can choose the optimal time and hospital for surgery. The system is managed by the Day Case Surgical Department. Available times and locations for surgery during a 6-month period are presented. Surgical capacity that has not been booked within two weeks of the relevant date is withdrawn and offered to patients who are not participating in the trial.

Patient information form: A patient information form (printable, integrated in the electronic health record) was prepared by a specialist in gastrointestinal surgery. The form included information about the place and time for surgery, information about the surgical procedure, and advice for the patient following surgery. Information about possible complications of surgery was also provided.

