##### Logistics

For patients who are included, the GP must follow certain steps to avoid trial bias. However, it is important that the procedures for enrolling patients in the trial are not so time-consuming that GPs choose not to include patients. The steps in the inclusion process will be:

1. Identify patients who meet the inclusion criteria according to guidelines provided in the electronic health record.

2. Obtain written informed consent from all eligible patients.

3. Call the randomisation centre at the University Hospital. The patient is then registered in the study database and thereby automatically randomised to either the one-stop approach or the traditional patient pathway.

4. If the patient is randomised to the intervention group, the standardised referral forms provided by the electronic health record must be used. If the patient is randomised to the control group, the traditional referral forms (also provided y the electronic health record) with no mandatory information regarding the specific disease must be used.

5. If randomised to the intervention group: book place, time and date of surgery

6. Print the information form about the surgical procedure and where and when to meet for surgery and give to the patient.

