##### Sample size

To calculate the sample size needed, we identified all patients who had undergone the specified surgical procedures within three months of normal surgical activity (September, October and November 2007). Of these 33 patients, 22 patients could be included in a one-stop protocol. The rest of the patients were not eligible due to different patient pathways.

We calculated the average waiting time from referral to examination at the surgical outpatient dept, the waiting time from outpatient examination to surgery, and the total waiting time (Table 2).

**Table 2 T2:** Mean waiting time for examination and surgical treatment for selected day case prcedures at a University Hospital during a three-month period of normal activity.

	GP referral to examination at the surgical outpatient clinic (days)	Internal hospital referral to day case surgery (days)	Total waiting time (days)
Waiting time^a ^(mean)	122	119	241
Standard deviation	118	92	154

^a ^Inguinal hernia, pilonidal sinus and uncomplicated gallstone disease

Based upon calculations in Table 2, we assume that there is no significant difference in waiting time between the three groups. Alpha and beta were set at 0.05 and 0.2 respectively. We estimate that a significant decrease in mean waiting time for surgery would be 60 days. The standard deviation is estimated as 120 days. We assume an exclusion rate of 20%, so that a sample size of 60 patients in each group is required.

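### The waiting-time clock starts at the hospital's noting of the referral, an event after randomisation and after an arm-specific referral step; starting at randomisation would remove a possible arm-dependent offset

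*Protocol article*

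**What the plan says.** Under Outcome measures, Waiting time for outpatient surgery, the protocol article rejects the health authorities' figures as unreliable and says that "waiting time must therefore be calculated separately for each individual using dates from the electronic health record". Three dates are named: the hospital's noting of the referral, the outpatient examination (control group only) and the surgery. The earliest, and so the start of the clock, is "the date the referral is noted in the hospital electronic health record".

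Logistics lists the inclusion steps in order. Identification and consent come first. The GP then telephones the randomisation centre: "The patient is then registered in the study database and thereby automatically randomised to either the one-stop approach or the traditional patient pathway". The referral follows, and its form depends on the allocation. For one-stop, "If the patient is randomised to the intervention group, the standardised referral forms provided by the electronic health record must be used". For control, "the traditional referral forms (also provided y the electronic health record) with no mandatory information regarding the specific disease must be used".

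In the one-stop arm, according to Intervention, "booking is done at the same time as referral", through a system that the Day Case Surgical Department manages. According to Control arm, control patients are referred to the surgical outpatient clinic. The Analysis section lists dates of referral, examination and surgery, but no date of randomisation, and promises an intention-to-treat analysis.

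**The concern.** In a randomised comparison of elapsed time, time zero should not be open to influence by the allocation. Here it is an administrative entry made after allocation, and the two arms reach it with different forms sent to different destinations. Time between randomisation and that entry is not counted. If more such time passes in one arm than in the other, the measured difference contains an offset that does not come from the wait itself, and a larger sample does not remove it.

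The sign is open. A longer lag in the control arm shortens the measured control wait and hides benefit. A longer lag in the one-stop arm, for example because a GP completes mandatory fields or pre-operative tests before sending, shortens the measured one-stop wait and exaggerates benefit. The protocol does not say that either happens, but the definition does not guard against it.

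There is also a smaller point. A randomised patient whose referral is never noted at the hospital has no time zero, which fits poorly with the promised intention-to-treat analysis.

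**Working it through.** **Order of events.** Reading Logistics against the outcome definition gives, for each patient: consent; randomisation and registration; arm-specific referral (with booking for one-stop); noting at the hospital; surgery. Noting cannot come before the referral, and the referral comes after randomisation. The start date is therefore a post-randomisation event in both arms.

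**Effect on the estimate.** Let *W* be the wait from randomisation to surgery and *L* the lag from randomisation to noting. The protocol measures *W* − *L*. Then

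measured reduction = (mean *W* control − mean *W* one-stop) − *b*, where *b* = mean *L* control − mean *L* one-stop.

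A lag common to both arms cancels. Only the differential *b* matters, and it acts day for day.

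**Inputs.** The Sample size section gives a difference of 60 days, SD 120 days, alpha 0.05, beta 0.2, a 20% exclusion rate and 60 patients per group. The Analysis section refers to two-sided tests at 0.05. No value of *b* is given, so the values below are assumptions.

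**The plan's own figure.** A two-sided test needs 2 × (1.960 + 0.842)² × (120/60)² = 62.8, so 63 per arm, or 63/0.8 = 78.75, so 79 after allowing for 20% exclusion. The stated 60 is matched by a one-sided 5% test with the exclusion rate added on: 2 × (1.645 + 0.842)² × 4 = 49.5, so 50, and 50 × 1.2 = 60. That discrepancy is a separate matter. The present point does not depend on it.

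**Sensitivity to *b*.** With 60 analysed per arm, the standard error of the difference is 120 × √(2/60) = 21.9 days. Two-sided power is Φ(measured difference/21.9 − 1.96).

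| Assumed *b* (days) | Measured difference (true 60) | Power, 60 per arm |
|---|---|---|
| −14 | 74 | 92% |
| −7 | 67 | 86% |
| −3 | 63 | 82% |
| 0 | 60 | 78% |
| 3 | 57 | 74% |
| 7 | 53 | 68% |
| 14 | 46 | 56% |

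For negative *b* the higher power is not a gain, because it comes from an inflated difference. If there were no true difference, an offset of 3, 7 or 14 days in either direction would give a two-sided error rate of about 5.2%, 6.2% or 9.8% instead of 5%. With the clock at randomisation, *b* drops out and the first row that applies is *b* = 0.

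**The case against.** The strongest reply is that nothing in the protocol shows a material lag. Study design and Randomisation both place randomisation at the time of referral. Both forms come from the same GP record system, and the Discussion says that referrals in North Norway are sent electronically. Data gathering says that data are collected identically in the two groups. On this text the lag should be short in both arms and its differential shorter still. At 3 days the offset is 3/21.9 = 0.14 standard errors, which is negligible. A hospital-registered date, applied by one rule to both arms, is also auditable and defensible.

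Most of this stands, and it limits the expected size. It does not show that the differential is zero, and it gives no reason to prefer a post-allocation date when an arm-neutral one should be available.

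A reader might be tempted by stronger readings, which the protocol does not support:

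- *That the lag does differ by arm.* No section gives a lag. The three weeks in Background for a hospital doctor to read a referral concern handling, not noting. Nothing suggests that a referral is noted only after that step, so this time appears to fall inside the measured wait.
- *That Table 2 uses a different start.* Its column label speaks of GP referral, and the text says "We calculated the average waiting time from referral to examination at the surgical outpatient dept". The label serves to distinguish this referral from the internal hospital referral in the next column. It does not say which date stamp was used.
- *That the current clock breaks randomisation.* It leaves the allocated groups as they are. At most it adds an offset of unknown size and sign.
- *That the randomisation date is certainly on file.* The protocol says only "The patient is then registered in the study database and thereby automatically randomised". Storage of the date is a reasonable inference from this, not a stated data item.

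**Conclusion.** The point holds as a structural weakness in the definition of a primary endpoint. Time zero follows randomisation and an arm-specific step, so any differential lag passes straight into the primary difference. Its size is unknown and may be small. A 7-day differential, which is an assumption and not an estimate, would move a 60-day difference to 53 days (power 78% down to 68% with 60 analysed per arm, SD 120, two-sided 5%) or up to 67 days. The direction cannot be stated in advance. The case for change rests on the ease of removing the possibility, not on evidence that bias is present.

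**What to change.** Define waiting time in both arms as the interval from the date of randomisation to the date of outpatient surgery. Confirm that registration at the randomisation call stores that date for every patient, and add it as a named data item if it does not. Keep the hospital noting date, and report the interval from randomisation to noting by arm as a descriptive component, so that readers can see whether the referral routes differ. List the randomisation date among the dates in the Analysis section.

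The cost is a change of wording and, at most, one extra date field. The design difference of 60 days and the sample-size inputs are unaffected. Every randomised patient then has a defined time zero for the intention-to-treat analysis. If the lag proves trivial, nothing is lost.
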